### Monitored parameters and data collection

The coordinating center of the CAPCTG will be responsible for data safety, privacy, and quality of the study conduct. Data collection and storage will use a web-based electronic database (Unimed Scientific, Wuxi, China). All data are input by the nominated investigator at each participating site. Training for data entry was arranged by the CAPCTG coordinating center before the study commencement. For the secondary endpoints requiring subjective assessments, all site investigators underwent centralized training on outcome assessment. The data required to be collected during different phases are shown in Figure 1.

**Figure 1 fig1:**
[figure not shown]
Schedule of enrollment, interventions, and assessments. PASS denotes pancreatitis activity scoring system. SOFA denotes sequential organ failure assessment.

### Statistical analysis

The reporting and presentation of this trial will follow the CONSORT guidelines (27). Primary analyses will be based on the intention-to-treat (ITT) population, and secondary supportive analyses will be done on the Per-protocol (PP) population. The safety analysis will be performed on the safety population (the same as the ITT population). Missing primary outcomes will be assumed to be missing at random (MAR) and thus will be ‘ignored’ in the primary analysis. However, if greater than 5% of all primary outcomes that should be available for analysis are missing, a series of sensitivity analyses after imputing the missing primary outcome will be undertaken in addition to the primary analysis. The ITT population consists of all randomized subjects, regardless of whether they are ineligible, prematurely discontinue treatment, or are otherwise protocol violators/deviators. The PP population is a subset of the ITT population that excludes those with major protocol deviations. Major protocol deviations will be defined in the statistical analysis plan.

The normality of continuous variables was examined using skewness and kurtosis. Continuous data were expressed as mean±standard deviation or median (interquartile range). Categorical data were expressed as numbers and percentages. A generalized linear mixed model that accounts for the random effect of different participating sites, and adjusted for several clinically important covariates will be employed to compare group differences in the primary outcome. The detailed analysis strategies for secondary outcomes and subgroup analyses by APACHE II score ≥8 (yes and no), CRP > 150 mg/L (yes and no), etiologies of AP (hypertriglyceridemia and non-hypertriglyceridemia), the presence of organ failure (yes and no), presence of shock (yes and no), and time interval between abdominal pain onset and enrollment ≤ 24 h (yes and no) will be included in the statistical analysis plan. Statistical tests will be two-sided, and *p* values <0.05 will be deemed statistically significant.

### Adverse events

All adverse events (AEs) occurring from the time of randomization to the final follow-up visit on day 90 will be reported to the CAPCTG coordinating center. AEs are defined as any untoward medical occurrence in a patient who received an investigational intervention. A serious adverse event(SAE) is defined as any serious medical event that causes death, life-threatening conditions, prolonged hospital stay, persistent disability or dysfunction, or other unpredictable serious medical events. The causal relationship between the AEs and the study drug will be classified as probable, possible, or unlikely (28). All AEs were systematically evaluated by the investigators to determine their potential relationship to the study intervention. In particular, bradycardia (heart rate <50 bpm) with hemodynamic compromise requiring intervention, significant hypotension requiring intervention, and arrhythmia with hemodynamic compromise requiring intervention would be recorded, and the association with treatment will be assessed.

An independent data safety and monitoring board (DSMB) (consisting of a surgeon, an intensivist, and a statistician) will oversee all aspects of patient safety based on reported AEs. No formal interim analysis was planned due to the limited sample size of the trial. The DSMB will review the AEs every 6 months, and it can call for a meeting for reported SAEs whenever deemed necessary during the trial. AEs will be reported in a uniform format through the electronic data capture system.

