### Study interventions

The study protocol only determines whether or not to use esmolol.

Group 1: Esmolol group

Patients will receive esmolol infusion within 1 h of randomization, starting at 25 mg/h, titrated to maintain a heart rate of 80–94 bpm, with a maximum dose of 0.2 mg/kg/min. The infusion will continue for 96 h unless: (1) the heart rate decreases below 80 bpm and re-evaluation needs to be performed after 20 min; (2) systolic blood pressure falls below 90 mmHg; (3) severe arrhythmias develop; or (4) the clinician deems it necessary based on the patient’s condition.

Meanwhile, we will implement stringent measures to mitigate the risk of low cardiac output in the study patients, including: (1) adequate fluid resuscitation prior to esmolol initiation; (2) patients assigned to the esmolol group had their blood pressure monitored every 15 min. and (3) cardiac output monitoring when necessary, using techniques like echocardiography, invasive hemodynamic monitoring, etc., as judged by the treating physicians.

Group 2: Standard care group

Patients will receive standard care without a placebo at the discretion of the treating physicians.

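### The adverse event definition, read literally, leaves out the standard care arm and contradicts the all-randomised safety population, so control-arm events may be under-reported

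*Protocol article*

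**What the plan says.** The Adverse events section of the protocol article opens with a reporting rule: "All adverse events (AEs) occurring from the time of randomization to the final follow-up visit on day 90 will be reported". The next sentence says what counts: "AEs are defined as any untoward medical occurrence in a patient who received an investigational intervention". A separate sentence covers serious events: "A serious adverse event(SAE) is defined as any serious medical event that causes death, life-threatening conditions, prolonged hospital stay". Bradycardia, hypotension and arrhythmia of a stated severity are singled out; the sentence ends "arrhythmia with hemodynamic compromise requiring intervention would be recorded, and the association with treatment will be assessed". Causality is graded on a three-level scale of relation to the study drug. The DSMB "will oversee all aspects of patient safety based on reported AEs", and no formal interim analysis is planned.

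Under Study interventions, the comparator arm is described thus: "Patients will receive standard care without a placebo at the discretion of the treating physicians".

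Under Statistical analysis: "The safety analysis will be performed on the safety population (the same as the ITT population". That population is defined in turn: "The ITT population consists of all randomized subjects, regardless of whether they are ineligible, prematurely discontinue treatment".

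**The concern.** A definition of an adverse event tells sites what to enter. This one makes receipt of the investigational intervention a condition, and in this trial the only intervention the protocol allocates is esmolol. Half of the safety denominator therefore falls outside the literal definition of the events to be counted.

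Hypotension, arrhythmia and death also occur in this disease without esmolol. A count of such events on esmolol can be interpreted only against a control count collected in the same way. The comparison matters here: the Introduction reports that a trial of a related β-blocker in septic shock was halted early with indications of potential mortality harm, and it concedes that β-blockade might reduce cardiac output. If control-arm events are collected less completely, the final safety table and the DSMB's reviews during the trial are both distorted. An analysis plan cannot recover events that were never recorded.

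**Working it through.** No figure in the plan depends on this point, so the check is a comparison of the statements, followed by what algebra allows on size.

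**Step 1: who meets the AE definition as written.**
- Standard care patients: no study drug and no placebo (Study interventions). Not covered.
- Patients allocated esmolol but never dosed: not covered.
- Patients allocated esmolol and dosed: covered.

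**Step 2: who is in the safety analysis.** Safety population = ITT = all randomised subjects, planned as 73 + 73 = 146 (Sample size, centers, and recruitment). At most about 73 of these, the esmolol recipients, meet the definition in step 1. The event definition and the denominator do not match.

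**Step 3: whether the neighbouring sentences settle it.**
- Reporting window: starts at randomisation, not at first dose, and names no arm. This points to collection in both arms. But it says when AEs are reported, and the next sentence says what an AE is.
- SAE definition: refers to any serious medical event and sets no condition of having received the intervention. It covers both arms.
- Bradycardia, hypotension and arrhythmia sentence: no arm restriction. It can be read as covering both arms, although the causality scale just before it refers only to the study drug and has no category for a patient who received none.
- Secondary endpoints: in-hospital and 90-day mortality, new organ failure and new vasoactive treatment are outcomes in both arms.

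Deaths and serious events are therefore covered in both arms, and the listed cardiac and haemodynamic events probably are. The exposed part is the remaining AEs, chiefly non-serious ones.

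**Step 4: direction of any bias.** The trial is open-label, so the site staff who enter events know who is a control. Study interventions states 15-minute blood pressure checks for the esmolol group only, so hypotension is also more likely to be noticed there. Both features act in the same direction: fewer recorded events in controls.

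**Step 5: size.** Let p be the true risk of an event, equal in both arms, and c the fraction of control events recorded relative to the esmolol arm.

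Apparent risk difference (esmolol minus control) = p − c·p = p(1 − c).

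- c = 1 (same collection in both arms): difference 0.
- c = 0 (no control events entered): difference p.

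As an assumption only, p = 20% gives 0.20 × 73 = 14.6 expected events per arm and an apparent difference somewhere between 0 and 20 percentage points, depending on c. The document gives neither p nor c. It supports the sign of the bias, but not its size.

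**The case against.** The strongest reply is that one loosely worded sentence is being set against a design that plainly includes controls. Reporting runs from randomisation, the safety set is everyone randomised, serious events are defined without reference to treatment, and the cardiac and haemodynamic events of interest are to be recorded with no arm named. Mortality, organ failure and vasoactive treatment are endpoints regardless of the AE wording. Nothing shows that any site has failed to enter a control's events. The layout of DSMB reports belongs to a charter or full protocol that is not shown.

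Most of this stands, and it limits the point. A reader might infer that controls can have no AEs at all, that the safety comparison has no comparator, or that the DSMB could not see excess mortality. The document does not support those readings. The SAE wording brings control-arm deaths and life-threatening events into reporting, and the DSMB may call a meeting on reported SAEs. The extreme case of zero recorded control events would require every site to ignore the rest of the section and the stated safety population.

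The reply does not remove the contradiction. Making the safety set equal to ITT fixes who is counted, not what is collected; if control events are missed, it adds patients with falsely few events. The endpoints protect the final comparison of deaths and organ support, but the article does not say that endpoint data reach the DSMB during the trial, whereas it does say that oversight rests on reported AEs.

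**Conclusion.** The point holds as an internal contradiction of moderate weight. The AE definition, read literally, excludes the standard care arm and undosed esmolol patients, while the safety population and the reporting window include them. The consequence is a risk of unequal ascertainment, mainly of non-serious events, with a bias towards an apparent excess on esmolol. This rests on one assumption, that some sites follow the definition as written. The size is not derivable from the document.

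A reader might go on to infer that the safety set will be tabulated as randomised, so that non-receipt and crossover dilute the drug's risks. The Statistical analysis section says who is in the set, not whether they are shown as allocated or as treated. That detail is commonly left to the analysis plan, and no rates of non-receipt or crossover are given. It forms no part of this finding.

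**What to change.** Redefine an AE as any untoward medical occurrence in any randomised participant, in either arm, from randomisation to day 90, whether or not esmolol was given. State that the listed bradycardia, hypotension and arrhythmia events are recorded in the same way in both arms. Tabulate AEs and deaths by arm in the reports to the DSMB.

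Ask sites to check that AEs of controls already enrolled were entered. With 73 patients recruited by December 2024 and equal allocation, that is about 73 / 2, or roughly 36 to 37 controls at that date, plus those recruited since.

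The cost is a change of protocol wording and a reminder to sites, with the check of existing control records. The design, sample size and endpoints are unaffected.

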## Introduction

Acute pancreatitis (AP) is a systemic inflammatory disease with significant morbidity, and about 20% of patients, who have more intense inflammation, develop severe AP (SAP) (1, 2). The inflammatory response, combined with intense stress and pain, leads to elevated sympathetic activation in SAP patients (3). In turn, the persistent excitation of the sympathetic nervous system can reciprocally intensify inflammation, triggering the release of inflammatory mediators and perpetuating a vicious cycle (4).

Given that sympathetic activation is a hallmark of inflammatory diseases (5, 6), numerous efforts have been undertaken to modulate its activity in the hope of improving clinical outcomes (7, 8). Recent studies suggest that modulating sympathetic nerve activity using *β*-1 adrenergic blockers may offer therapeutic benefits in sepsis by attenuating excessive inflammatory responses and organ failure (6, 9). Esmolol, a short-acting intravenous *β*-blocker, was previously used to treat inflammatory conditions like sepsis (10, 11). It works by inhibiting the effects of adrenaline on sympathetic overactivation, thereby reducing heart rate to improve tissue perfusion and suppressing inflammatory mediators (12).

A phase II clinical trial involving 154 patients with septic shock demonstrated that esmolol could reduce heart rate without affecting mean arterial pressure (13). Notably, esmolol significantly reduced 28-day mortality (49.4% in the esmolol group vs. 80.5% in the control group, *p* < 0.001) (13). Another study in 2015 found that combining milrinone and esmolol improved cardiac function and 28-day survival in patients with severe sepsis (14). Recently, two large-scale trials were published testing the effects of a new ultra-short-acting *β*-blocker, landiolol, in patients with septic shock and persistent tachycardia [The Landi-SEP (15) and STRESS-L (16)]. The former found that landiolol was effective in reducing and maintaining heart rate without increasing vasopressor requirements after 24 h. However, the latter was halted prematurely after enrolling only 37% of the planned participants. The decision was made due to the lack of evidence suggesting that landiolol could improve organ function, coupled with indications of potential mortality harm. The most likely explanation, as the authors suggested, may be compromised cardiac output in patients with already existing shock.

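### The adverse-event definition, read literally, leaves out the control arm, so the DSMB could lack the comparator it needs to judge an excess of deaths

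*Protocol article*

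**What the plan says.** All of the following is in the protocol article.

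- **Interim analysis** (Adverse events): "No formal interim analysis was planned due to the limited sample size of the trial".
- **DSMB** (Adverse events): an independent board, "consisting of a surgeon, an intensivist, and a statistician", which "will oversee all aspects of patient safety based on reported AEs". On timing: "The DSMB will review the AEs every 6 months, and it can call for a meeting for reported SAEs whenever deemed necessary during the trial".
- **Reporting window** (Adverse events): events "occurring from the time of randomization to the final follow-up visit on day 90 will be reported to the CAPCTG coordinating center".
- **Definitions** (Adverse events): "AEs are defined as any untoward medical occurrence in a patient who received an investigational intervention". A serious adverse event "is defined as any serious medical event that causes death, life-threatening conditions, prolonged hospital stay", among other criteria.
- **Control arm** (Study interventions): usual care at the physicians' discretion, with no placebo. The only thing that the protocol fixes is whether esmolol is used.
- **Safety population** (Statistical analysis): identical to the ITT population, which is every randomised subject.
- **Known hazard** (Introduction): a landiolol trial in septic shock stopped at 37% of planned enrolment because organ function was not improving, "coupled with indications of potential mortality harm".

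**The concern.** With no formal interim analysis, the DSMB's review of adverse events is the only scrutiny of accruing safety data that the article describes. What that review can show depends on what is reported to it. If reporting follows the printed definition, the board sees events in patients given esmolol and may see few or none from the standard-care arm.

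Deaths and organ failure are expected in predicted severe acute pancreatitis whatever the treatment. Case-by-case attribution (probable, possible or unlikely), made by unblinded investigators in an open-label trial, cannot separate a moderate drug-related excess from that background. Only a comparison by arm can. The article itself cites a trial in the same drug class that stopped partly on a mortality signal, so this is a question that the board should be able to answer.

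The final safety analysis is also at stake. If adverse events are collected more completely on esmolol than on standard care, the between-arm comparison in the safety population is biased against esmolol for non-fatal events, however the analysis is done.

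**Working it through.** **1. Who is covered, statement by statement**

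| Place in the article | Who is covered |
|---|---|
| Adverse events, definition of an AE | Patients who received an investigational intervention |
| Adverse events, reporting window | Starts at randomisation, not at first dose |
| Adverse events, causality | Relation to the study drug |
| Adverse events, DSMB remit | Reported AEs |
| Study interventions | Controls receive standard care, no placebo |
| Statistical analysis, safety population | All randomised patients, both arms |

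The first and last rows cannot both govern data collection. Under the first, a control patient has no reportable AE, and neither has a patient allocated to esmolol who never received it. Under the last, both are analysed for safety.

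**2. Why the comparator matters**

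Hypothetical counts with 37 patients per arm and a pooled z-test, z = (d₁ − d₀)/37 ÷ √[p(1 − p)·2/37], where p = (d₁ + d₀)/74:

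- 10 deaths on esmolol, 2 on control: p = 0.162, difference 0.216, standard error 0.0857, z = 2.52.
- 10 deaths on esmolol, 8 on control: p = 0.243, difference 0.054, standard error 0.0997, z = 0.54.

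The esmolol count is the same in both. Only the control count tells them apart.

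**3. The plan's own size, and what it allows**

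From Sample size: SD 4.1, difference 2 days, 80% power; two-sided 0.05 from Statistical analysis. n = 2(1.960 + 0.842)² × 4.1²/2² = 65.97, so 66 per group. Then 66 × 1.10 = 72.6, so 73 per group and 146 in all. The stated figure reproduces. It is driven by organ-failure-free days, not by mortality.

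The article gives no mortality rate. Assume control mortality of 5–20% and an absolute excess of 10–20 points. Power of a two-sided 0.05 test on deaths is then:

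- 13–54% at 54 patients (37% of 146, the fraction at which the cited trial stopped);
- 16–67% at 72 patients;
- 29–93% at 146 patients.

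Small size therefore does limit what a formal look could find.

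**4. An optional harm guideline**

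Simulation: pooled z-test on deaths at 37 and 55 per arm (74 and 110 patients), one-sided p<0.01 for excess deaths on esmolol, all outcomes assumed known at each look. At the planned pace, 146 over about 23 months (6.3 a month), six-monthly reviews at months 12 and 18 would fall near 76 and 114 patients, so these looks are realistic.

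| Assumed mortality, control vs esmolol | Chance of a flag |
|---|---|
| 10% vs 10%; 20% vs 20% | 1–2% |
| 10% vs 20% | 21% |
| 15% vs 25% | 18% |
| 20% vs 30% | 16% |
| 10% vs 25% | 43% |
| 15% vs 35% | 58% |
| 10% vs 30% | 66% |

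The 43–66% band for a 15–20-point excess belongs to the three pairs shown. Re-running the same simulation (400,000 trials) at 15% vs 30% and 20% vs 35% gives 36% and 32%.

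**5. Cost in type I error**

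A by-arm safety table with no efficacy stopping gives no extra chance to claim benefit, so the final 0.05 stands. Even a formal two-sided p<0.001 look at half the information, with the final test kept at 0.05, gives an overall error of 0.0502.

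**The case against.** The strongest defence is that the definition is boilerplate and its context corrects it. Events count from randomisation, the safety population is all randomised patients, standard care is listed under Study interventions, the wording for serious events does not mention receipt of treatment, and mortality is collected in both arms as a secondary endpoint. Nothing says that control-arm deaths go unreported or that the DSMB sees esmolol data only. By-arm closed tables and harm guidelines normally sit in a charter, which is not shown. Much of this stands: the sites may well be reporting both arms, and the lack of a printed boundary is not an error. What does not fall away is that the printed definition and the safety population disagree, and that the DSMB's remit is tied to the narrower of the two.

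A reader might infer more: that a mortality signal has no planned route to detection, or that ruling out a formal interim analysis is itself a fault. The documents do not support either. Fatal events are serious adverse events, reporting runs to day 90, and an independent board with a statistician meets every six months and can meet in between. Ruling out a formal interim analysis does not rule out by-arm safety tables. Nor do the documents establish excess death as a settled effect of the drug class: the Introduction also reports lower 28-day mortality with esmolol in septic shock (49.4% vs 80.5%), and it offers reduced cardiac output only as the likely explanation of one trial's result in patients already in shock.

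**Conclusion.** The point holds as an inconsistency in the printed text with a safety consequence. The AE definition, read literally, excludes the standard-care arm; the safety population includes it; and DSMB oversight is based on reported AEs. If sites follow the definition, the board lacks the comparator needed to judge an excess of deaths. Whether they do cannot be told from the article.

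The size of the consequence cannot be fixed, because no mortality rate is given. A numerical harm rule would be of modest value: under the assumed rates it would miss about four in five trials with a 10-point excess, and somewhat more than that in practice, since late deaths would not all be known at each look. It is a matter of judgement for the charter. Complete by-arm reporting does not depend on any of these assumptions.

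**What to change.** 1. Reword the AE and SAE definitions and the reporting instruction to cover every randomised patient in both arms, from randomisation to day 90, whether or not esmolol was given. This brings them into line with the safety population.
2. State that at each six-monthly review already scheduled the DSMB receives a closed by-arm table of deaths and new organ failure for all randomised patients.
3. State that there is no stopping for efficacy, so the final two-sided 0.05 is unchanged.
4. Optionally, put a non-binding harm guideline in the DSMB charter, for example one-sided p<0.01 for excess deaths on esmolol, with its operating characteristics under stated mortality assumptions.

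The cost is one closed table per review and fuller AE reporting in the control arm. Deaths and organ failure are already collected as endpoints, and the board already includes a statistician. Because 73 patients had been recruited by December 2024, the sponsor should also check whether control-arm events were reported for patients already enrolled, and complete them from the records where they were not. If the optional guideline is adopted, it carries a 1–2% chance of a false flag under the assumed rates, which the board may override.
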